| Statistical Considerations:            | 
For the main outcome, we estimated a sample size of 42 participants (21 in each arm), assuming 80% power and a two-sided type I error rate of 5% to reject the null hypothesis. The following assumptions were made: a baseline standard deviation (SD) for TIR of 15%, a pre-post difference in TIR of 0.2% in the control group, a pre-post difference of 10.5% in the treatment group, a correlation of 0.7, and a dropout rate of 20%.
                                                                                                                                                                                                                                                                                                                                                                                                                                                                                                                                                                                                                                                                                                                                                                                                                                                                               |
| GCP Statement:                         | 
This study will be conducted in compliance with the protocol, the current version of the Declaration of Helsinki, ICH-GCP, and all national legal and regulatory requirements.
                                                                                                                                                                                                                                                                                                                                                                                                                                                                                                                                                                                                                                                                                                                                                                                                                                                                                                                                                                                                                                                                                                                                           |

**ABBREVIATIONS**

|       |                                                                                                                                                           |
|-------|-----------------------------------------------------------------------------------------------------------------------------------------------------------|
| AE    | Adverse Event                                                                                                                                             |
| ASR   | Annual Safety Report                                                                                                                                      |
| AID   | Automatic Insulin Delivery                                                                                                                                |
| BASEC | Business Administration System for Ethical Committees,
( https://submissions.swissethics.ch/en/ ) |
| BIA   | Bioelectrical Impedance Analysis                                                                                                                          |
| BMI   | Body Mass Index                                                                                                                                           |
| BP    | Blood Pressure                                                                                                                                            |
| CA    | Competent Authority (e.g. Swissmedic)                                                                                                                     |
| CAP   | Controlled Attenuation Parameter                                                                                                                          |
| CEC   | Competent Ethics Committee                                                                                                                                |
| CRF   | Case Report Form                                                                                                                                          |
| CRA   | Clinical Research Associate                                                                                                                               |
| ClinO | Ordinance on Clinical Trials in Human Research ( in German: KlinV, in French: OClin, in Italian: OSRUm )                                           |
| CTCAE | Common terminology criteria for adverse events                                                                                                            |
| CGM   | Continuous Glucose Monitoring                                                                                                                             |
| CVD   | Cardiovascular Disease                                                                                                                                    |
| DCB   | Diabetes Center of Bern                                                                                                                                   |
| DIO   | Diet-induced obese                                                                                                                                        |
| DKA   | Diabetic ketoacidosis                                                                                                                                     |
| DTSQ  | Diabetes Treatment Satisfaction Questionnaire                                                                                                             |
| ECG   | Electrocardiogram                                                                                                                                         |
| eCRF  | Electronic Case Report Form                                                                                                                               |
| eGFR  | Estimated Glomerular Filtration Rate                                                                                                                      |
| GCP   | Good Clinical Practice                                                                                                                                    |
| GIP   | glucose-dependent insulinotropic polypeptide                                                                                                              |
| GIPR  | GIP receptor                                                                                                                                              |
| GLP   | Glucagon-like Peptide                                                                                                                                     |
| GMP   | Good Manufacturing Practice                                                                                                                               |
| Ha    | Alternative Hypothesis                                                                                                                                    |
| Ho    | Null hypothesis                                                                                                                                           |
| HR    | Heart Rate                                                                                                                                                |
| HRA   | Federal Act on Research involving Human Beings ( in German: HFG, in French: LRH, in Italian: LRUm )                                                |
| IB    | Investigator's Brochure                                                                                                                                   |
| IMP   | Investigational Medicinal Product                                                                                                                         |
| IIT   | Investigator-initiated Trial                                                                                                                              |

|       |                                                          |
|-------|----------------------------------------------------------|
| ISF   | Investigator's Site File                                 |
| ITT   | Intention to treat                                       |
| LSM   | Liver Stiffness Measurement                              |
| MASH  | Metabolic dysfunction-associated steatohepatitis         |
| MASLD | Metabolic Dysfunction-Associated Steatotic Liver Disease |
| PI    | Principal Investigator                                   |
| PP    | Per Protocol                                             |
| SC    | Subcutaneous                                             |
| SDV   | Source Data Verification                                 |
| SoC   | Standard of Care                                         |
| SOP   | Standard Operating Procedure                             |
| SPC   | Summary of product characteristics                       |
| SUSAR | Suspected Unexpected Serious Adverse Reaction            |
| TDI   | Total Daily Insulin                                      |
| TMF   | Trial Master File                                        |
| T1D   | Type 1 diabetes                                          |
| T2D   | Type 2 diabetes                                          |
| UPN   | Unique Patient Number                                    |

**SUMMARY OF THE REVISION HISTORY IN CASE OF AMENDMENTS**

| Version Nr,
Version Date  | Chapter        | Description of change                                   | Reason for the change                |
|------------------------------|----------------|---------------------------------------------------------|--------------------------------------|
| 1.0
(date:
18.09.2024) | Not applicable | Initial document                                        | Not applicable                       |
| 1.1
(date
04.11.2024)  | Not applicable | Harmonization, AE/SAE reporting, and outcomes (updated) | Swissmedic and BASEC ethics requests |

**STUDY SCHEDULE****Table 1. Visit Schedule.**

|                                                                             | Screening | Randomization             | Treatment Period |    |    |    | Follow-up       |
|-----------------------------------------------------------------------------|-----------|---------------------------|------------------|----|----|----|-----------------|
| Visit (V) or Phone (P)                                                      | V1        | V2                        | P1               | V3 | P2 | V4 | P3 a |
| Weeks                                                                       | -2        | 0                         | 4                | 8  | 12 | 16 | 18              |
| Window (days)                                                               | -7        | 14 up to 21 days after V1 | ±3               | ±3 | ±3 | ±3 | ±7              |
| Subject-related information/ assessments                                    |           |                           |                  |    |    |    |                 |
| Informed consent                                                            | X         |                           |                  |    |    |    |                 |
| Inclusion/Exclusion                                                         | X         |                           |                  |    |    |    |                 |
| Randomization                                                               |           | X                         |                  |    |    |    |                 |
| Screen fail/withdrawal criteria                                             | X         | X                         | X                | X  | X  | X  |                 |
| Medical history/demography b                                     | X         |                           |                  |    |    |    |                 |
| Concomitant medications                                                     | X         |                           |                  |    |    |    |                 |
| Trial-related outcomes measures and downloads                               |           |                           |                  |    |    |    |                 |
| Weight, Height, Waist & Hip circumference                                   | X         |                           |                  | X  |    | X  |                 |
| Vital signs (BP, HR, Temperature c )                             | X         | X                         |                  | X  |    | X  |                 |
| ECG                                                                         | X         |                           |                  | X  |    | X  |                 |
| Body composition (BIA)                                                      |           | X                         |                  |    |    | X  |                 |
| Hepatic elastography (FibroScan®)                                           |           | X                         |                  |    |    | X  |                 |
| Device downloads (CGM and pump data)                                        |           | X                         | X                | X  | X  | X  |                 |
| SNAQ app data downloads                                                     |           | X                         |                  | X  |    | X  |                 |
| Activity tracker downloads                                                  |           | X                         |                  | X  |    | X  |                 |
| Questionnaires (DTSQs-c)                                                    |           | X                         |                  |    |    | X  |                 |
| AE/SAE assessment including assessment for clinical significance and severe | X         | X                         | X                | X  | X  | X  | X               |

|                                                                             |                |                |   |                |   |                |  |
|-----------------------------------------------------------------------------|----------------|----------------|---|----------------|---|----------------|--|
| hypoglycemia and DKA                                                        |                |                |   |                |   |                |  |
| Laboratory                                                                  |                |                |   |                |   |                |  |
| HbA1c (central)                                                             | X              |                |   |                |   | X              |  |
| Hematology (hb-hct)                                                         | X              |                |   |                |   |                |  |
| Serum/urine pregnancy test (for child-bearing potential women) d | X              | X              |   | X              |   | X              |  |
| Hepatic chemistry/coagulation                                               | X e |                |   | X f |   | X f |  |
| Endocrine                                                                   | X g |                |   |                |   | X h |  |
| Pancreas (exocrine) panel                                                   | X              |                |   | X              |   | X              |  |
| Lipid panel (fasting)                                                       | X              |                |   |                |   | X              |  |
| Glucose fasting                                                             | X              |                |   |                |   |                |  |
| Urine chemistry                                                             | X i |                |   | X j |   | X i |  |
| Supply, re-supply and instructions/training                                 |                |                |   |                |   |                |  |
| IMP dispensing/re-supply                                                    |                | X a |   | X              |   |                |  |
| Study phones k and activity trackers dispensing                  | X              |                |   |                |   |                |  |
| Ketone meter dispensing                                                     |                | X              |   |                |   |                |  |
| Dexcom G7 system dispensing/re-supply                                       | X              | X              |   | X              |   |                |  |
| Supplies l dispensing/re-supply                                  |                | X              |   | X              |   |                |  |
| Medication logbook handover                                                 |                | X a |   | X a |   |                |  |
| Hypoglycemia diary handover                                                 | X              | X              |   |                |   |                |  |
| Study handbook                                                              | X              |                |   |                |   |                |  |
| IMP instructions/training                                                   |                | X a |   |                |   |                |  |
| Ketone meter instructions/training                                          |                | X              |   |                |   |                |  |
| Study apps and activity tracker installation/instructions/training          | X              |                |   |                |   |                |  |
| Others                                                                      |                |                |   |                |   |                |  |
| IMP accountability/compliance check                                         |                |                |   | X              |   | X              |  |
| Medication logbook review and collection                                    |                |                |   | X              |   | X              |  |
| Hypoglycemia diary review                                                   |                | X              | X | X              | X | X              |  |
| Handout of documents/reminders                                              |                | X              | X | X              | X | X              |  |
| Return non-used pens of the IMP                                             |                |                |   |                |   | X              |  |
| De-installation study apps                                                  |                |                |   |                |   | X              |  |
| Return study devices (activity tracker, phones, and ketone meters)          |                |                |   |                |   | X              |  |

Abbreviations: BMI= body mass index; BG= blood glucose; BP = blood pressure; HR= heart rate; BIA= bioelectrical impedance analysis; CGM=continuous glucose monitoring; DTSQs-c= diabetes treatment satisfaction questionnaire status and change versions; ECG= electrocardiogram; U/S=unscheduled; P/D= premature discontinuation; DKA=diabetes ketoacidosis; HbA1c = hemoglobin A1c; Hb= hemoglobin; HCT= hematocrit; IMP=investigational medicinal product; FDA=Food and Drug

*Administration.*

aOnly for the participants in the intervention arm.

bIncluded: gender, race/ethnicity, and year of birth.

cThe temperature should be measured at the screening visit (V1) and randomization visit (V2) to exclude infection.

dA serum pregnancy test will be performed at the screening visit, the result must be available before randomization and the first injection of the study drug for women of childbearing potential only. Additional pregnancy in urine tests will be repeated during the study (**See annex 6-6.1**).

eInclude: total bilirubin, direct bilirubin, alkaline phosphatase (ALP), partial thromboplastin time (PTT), prothrombin time (PT), international normalized ratio (INR), alanine aminotransferase (ALT), aspartate aminotransferase (AST), and gamma-glutamyl transferase (GGT). (**See annex 6-6.1**).

fInclude: total bilirubin, direct bilirubin, ALT, AST. (**See annex 6-6.1**).

gInclude: thyroid stimulating hormone (TSH), free thyroxine (FT4), calcitonin, C-peptide (fasting), estradiol, and follicle-stimulating hormone (FSH) (**See annex 6-6.1**).

hOnly calcitonin (**See annex 6-6.1**).

iInclude: creatinine (with eGFR by CKD-EPI), and urine microalbumin/creatinine ratio (uACR) (**See annex 6-6.1**).

jOnly creatinine (with eGFR by CKD-EPI) (**See annex 6-6.1**).

kThe participant also can use her/his phone if it is compatible with Dexcom G7 and the study apps.

lInclude: test strips, lancing device, and lancets.

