### 3.2 Investigational Product (treatment) and Indication

Tirzepatide (*Mounjaro*®) is the first-class incretin mimetic with dual GIP and GLP-1 receptor agonism; its synthetic chemical structure is based on the GIP sequence consisting of 39-amino acid peptide but has been modified to include (i) substitution of the second amino acid with aminoisobutyric acid to avoid DPP-4 proteolysis and, (ii) addition of a C20 fatty di-acid acyl chain to enable non-covalent albumin binding and once-weekly subcutaneous dosing (52). Tirzepatide exhibits comparable binding affinity and potency at the human GIP receptor (GIPR) relative to the native GIP peptide. However, tirzepatide binds with 5-fold less affinity and is 13-fold less potent at the human GLP-1R than native GLP-1 (52).

The peptide is well absorbed after subcutaneous (SC) administration with a mean absolute bioavailability of 80%. Following an SC administration, tirzepatide plasma concentrations reach a peak serum concentration (Tmax) between 24 and 48 hours. The average half-life (t1/2) is ~5 days with an expected steady state within 4–5 weeks of therapy (53).

Tirzepatide bound in vitro highly to serum albumin (99%). In vivo metabolism and excretion studies with [C] tirzepatide showed that tirzepatide excretion is generated via proteolytic cleavage of the peptide backbone, β-oxidation of the C20 fatty acid moiety with and without taurine conjugation, and/or amide hydrolysis. Drug-related material was excreted via urine and feces (49% via urine, 35% via feces) (53,54).

Tirzepatide is currently authorized in Switzerland to treat adults with T2D or obesity in addition to diet and exercise. There is no current indication to use tirzepatide in T1D from the local authorities.

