g) *Risk of Hypoglycemia (Low Blood Glucose)*

As with any person with diabetes who uses insulin, there is always a risk of having low blood sugar (hypoglycemia) (88). GIP/GLP-1RA, such as tirzepatide (Mounjaro®), is known to improve insulin action and, therefore, may increase the risk for low blood glucose (**See Annexes 1 to 3** for the adjustment in the AID systems during the drug up-titration and treatment period). Symptoms of low blood glucose can include sweating, jitteriness, and not feeling well. There is also the possibility of fainting or seizures (convulsions), brain damage, or death with level 3 of hypoglycemia (80). The participants will be strictly monitored (as a part of the clinical study) for these symptoms. The frequency of hypoglycemia should be no more and possibly less than it would be as part of daily living. Low glucose levels can be quickly resolved with a hypoglycemic treatment (fast-acting carbohydrates). Severe low blood glucose may require the administration of intranasal glucagon (*BAQSIMI*®) or vial injection (*GlucaGen*® *HypoKit*®) and/or have emergency services to help raise the participant's blood glucose level (**See Annex 4 and 10** for the hypoglycemia risk mitigation plan and hypoglycemia classification).

h) *Risk of Hyperglycemia (High Blood Glucose)*

Hyperglycemia and ketone formation are always a recognized risk in people with T1D. Hyperglycemia and ketonemia could occur if insulin administration is attenuated or suspended for an extended period (88). Hyperglycemia usually does not cause obvious symptoms, but participants may become thirsty, fatigued, or have higher glucose levels in their urine. In severe cases of hyperglycemia, diabetic ketoacidosis (DKA) or coma may occur. Hyperglycemia leading to DKA can lead to renal failure (kidney failure), cardiac arrhythmia (irregular heartbeat), myocardial infarction (heart attack), rhabdomyolysis (muscle breakdown), and even death (94). A serious effect from hyperglycemia is not expected to occur in any study participant, as we will be monitoring blood glucose levels frequently (**See Annex 5** for Guidance on checking for ketones).

i) *Whole-body composition using bioelectrical impedance analysis (BIA)*

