### 8.6 Trial-specific Preventive Measures

A serum pregnancy (serum beta-Hcg) test will be performed for all female participants of childbearing potential at the screening visit as part of the eligibility assessment. The result must be available before randomization and the first injection of the study drug. Additional pregnancy in urine tests will be repeated during the study.

If pregnancy occurs after inclusion and during the ongoing study, it will be reported to the Sponsor within a maximum of 24 hours. Consequently, the pregnant participant will be withdrawn from the study (**See Annex 7**).

In addition, the study team will encourage the participants to obtain glucagon Intranasal (*BAQSIMI*®) or vial injection (*GlucaGen*® *HypoKit*®) through prescription. All participants must have glucagon products as part of the standard of diabetes care. The participant and their caregiver (if any) must be trained on using glucagon products (**See Annex 4**, hypoglycemia risk mitigation plan).

The study participants will receive a ketone meter (**See Annex 5** for Guidance on checking for ketones).

The use of any rescue medication and concomitant medications will be recorded in the eCRFs.

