#### Both randomization arms:

During this visit, the study team will perform the following evaluations.

- Weight, height, waist & hip circumference, waist-to-hip ratio
- Vital signs (blood pressure and heart rate)
- ECG
- Urine pregnancy test
- Device downloads (CGM and pump data)
- Apps Downloads (SNAQ App, activity tracker)

- AE/SAE assessment according to **Section. 10** (including assessment for clinically significant hypoglycemia, severe hypoglycemia, and DKA)
- The hypoglycemia diary will be collected and reviewed.
- Laboratory tests including total bilirubin, indirect and direct bilirubin, ALT, AST, pancreatic serum amylase, serum lipase, and creatinine with eGFR (calculated by CKD-EPI).

Intervention arm:

The participant's medication logbook will be reviewed, the IMP's used pen will be collected, and the study physician will configure the systems and pump's parameters if needed (**See Annex 3**).

### 9.3.5 Phone Visit 2

Both randomization arms:

During this visit, the study team will contact the participants by phone. The study staff ensures that the data from the devices (CGM and pump data) have been downloaded, the hypoglycemia diary reviewed, and perform the AE/SAE assessment, according to **Section 10**.

Intervention arm:

If needed, the study physician will configure the systems and pump's parameters (**See Annex 3**).

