### 9.3.6 Visit 4 – End of intervention

Both randomization arms:

During this visit, the study team will perform the following evaluations:

- Weight, height, waist & hip circumference, waist-to-hip ratio
- Vital signs (blood pressure and heart rate)
- ECG
- Body composition (BIA)
- MAFLD and Liver fibrosis assessment (FibroScan®)
- Urine pregnancy test
- Device downloads (CGM and pump data)
- AE/SAE assessment according to **Section. 10** (including assessment for clinically significant hypoglycemia, severe hypoglycemia, and DKA).
- The hypoglycemia diary will be collected and reviewed.
- Questionnaires (DTSQc), the participant will complete a paper questionnaire, and the study staff will enter the data in REDCap.
- Laboratory tests including total bilirubin, indirect and direct bilirubin, ALT, AST, pancreatic serum amylase, serum lipase, creatinine with eGFR (calculated by CKD-EPI), uACR, calcitonin, HbA1c, CT, LDL, HDL, and triglycerides.

At visit 4, all the study devices will be returned.

Intervention arm:

The participant's medication logbook will be reviewed and collected. As well as the IMP's used pens.

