## Annex 1. Guidance on the functionality of the automatic insulin delivery systems (AID).

Insulin delivery may be reduced by 20-30% during tirzepatide initiation by adjusting the specific AID modifiable parameters (carbohydrate–insulin ratio, correction factor, active insulin time or target glucose, etc) (See Annexes 1-2).

The study physician will be updated on the basic functionality of commercial AID systems, their adjustable settings, and troubleshooting per manufacturer's instructions. For further information please see **Table A1** and <https://www.pantherprogram.org/device-comparison-chart>

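### The study ketone meter is collected at week 16, about two weeks before the tirzepatide arm's safety follow-up ends (minor, cheap to fix)

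*Protocol*

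**What the plan says.** **Return of the meter.** In Table 1 the row "Return study devices (activity tracker, phones, and ketone meters" is marked only at V4, with no footnote that separates the arms. Section 9.3.6 agrees: "At visit 4, all the study devices will be returned". Section 8.10.5 places the return of the meters at the end of the study, without naming a visit.

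**Follow-up after V4.** The tirzepatide arm has a further call at week 18 ±7 days (P3 in Table 1, headed Phone Visit 4 in section 9.3.7). The AE/SAE row of Table 1, whose label includes DKA, is marked at P3. Sections 9.2.4 and 10.1.2 run adverse-event collection through the safety follow-up period.

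**Purpose of the meter.** Section 8.6, on trial-specific preventive measures, states: "The study participants will receive a ketone meter". Annex 5 requires every participant to have one, gives no end date, and sets its action steps by numeric ketone levels. Section 10.1.2 lists four routes by which a hyperglycemic event becomes reportable. The fourth is a blood ketone level of at least 2.5 mmol/L even when no provider was contacted.

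**Drug and device.** On tirzepatide, section 3.2 says: "The average half-life (t1/2) is ~5 days". Section 3.7 e says the meter is for one patient only and will not be shared.

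**The concern.** The protocol treats home ketone testing as a safety measure, yet withdraws the device before the safety follow-up of the treated arm is over. The weeks after the last dose are when the drug effect fades and the participant returns to insulin alone. Section 3.7 h gives the general background for watching ketones: "Hyperglycemia and ketonemia could occur if insulin administration is attenuated or suspended for an extended period".

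Two things would be at stake in that interval. The first is the participant's own sick-day check, because the Annex 5 steps cannot be followed without a reading. The second is capture of ketosis that the participant detects and manages alone, which in practice is what the fourth reporting criterion covers. No section exempts the tirzepatide arm from the return at V4 or supplies a replacement meter.

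**Working it through.** **1. Length of the gap.** Inputs from Table 1: V4 at week 16 ±3 days (day 112 ±3), P3 at week 18 ±7 days (day 126 ±7).
- Nominal: 126 − 112 = 14 days. This reproduces the interval of about two weeks in section 9.3.7.
- Shortest: (126 − 7) − (112 + 3) = 4 days.
- Longest: (126 + 7) − (112 − 3) = 24 days.
- If the call is instead timed from each participant's actual V4, the range is 14 ± 7 = 7 to 21 days.

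**2. Washout over the gap.** Input: half-life of 5 days (section 3.2). Assumptions: first-order decline and no dose after V4. Level at P3 relative to V4 = 0.5^(t/5).
- t = 14: 0.5^2.8 = 0.144, about 14%.
- t = 4: 0.5^0.8 = 0.574, about 57%.
- t = 24: 0.5^4.8 = 0.036, about 4%.

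At the nominal timing, most of the decline from the V4 level therefore falls in the period without the study meter.

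**3. Which reporting routes in section 10.1.2 need the study meter.**
- Criterion 1 (DKA): no. It requires treatment in a facility and accepts serum or urine ketones.
- Criterion 2 (acute event evaluated at a facility): no.
- Criterion 3 (ketones of at least 1.5 mmol/L with provider contact): weakened but not lost, since the contacted provider can measure ketones.
- Criterion 4 (ketones of at least 2.5 mmol/L without contact): in practice yes, because only a reading held by the participant can trigger it.

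**4. Exposure without the meter.** Input: 21 participants in the tirzepatide arm.
- Nominal: 21 × 2 = 42 person-weeks.
- Window limits: 21 × 4/7 = 12 and 21 × 24/7 = 72 person-weeks.
- With the 20% attrition of section 11.2: 21 × 0.8 × 2 = 33.6 person-weeks.

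**5. Expected events.** Section 9.2.5 cites a DKA incidence of 4.8% but does not state the period. Assuming it is annual:
- Nominal: 42/52 × 0.048 = 0.039 cases; with attrition, 33.6/52 × 0.048 = 0.031.
- Window limits: 12/52 × 0.048 = 0.011 and 72/52 × 0.048 = 0.066.
- If 4.8% instead referred to three months: 42/13 × 0.048 = 0.155.

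These would be cases treated in a facility, so they would still be recorded. The protocol gives no rate for ketosis detected at home. For one criterion 4 event to be expected in the gap, the rate would have to be 52/42 = 1.24 per person-year, or 52/33.6 = 1.55 with attrition. That is 1.24/0.048 ≈ 26 to 1.55/0.048 ≈ 32 times the assumed annual DKA rate.

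**The case against.** Collecting devices at V4 is a coherent choice. Treatment ends there, it is the last on-site visit, and device downloads and hypoglycemia diary review also stop there. Section 6.1 evaluates safety endpoints at weeks 8, 12 and 16, so P3 is not an endpoint time point. The hyperglycemia outcome in chapter 5 counts rescue therapy and DKA episodes, neither of which is defined by a home reading. After V4 participants still have their own AID system and sensor, self-monitored glucose is routine care, and some may own a ketone meter. All of this stands. It is why the point is minor, and none of it supplies a home ketone reading to someone without a meter.

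A reader might go further and infer that participants enter washout with insulin settings still lowered. Annex 1 says "Insulin delivery may be reduced by 20-30% during tirzepatide initiation by adjusting the specific AID modifiable parameters", and the arm-specific text of section 9.3.6 begins with "The participant's medication logbook will be reviewed and collected" and lists no pump review. The documents do not support that inference. The reduction is optional and tied to initiation, and Annex 2 says some participants may need none. Settings can be revised at phone visit 1, at visit 3, and again at phone visit 2: "If needed, the study physician will configure the systems and pump's parameters". Annex 3 encourages review against glycemic goals after titration, and the systems in Annex 1 adjust delivery themselves. A review that is not listed at V4 is also not one that is ruled out, since pump data are downloaded at that visit.

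A reader might also see a contradiction between section 8.10.5 and Table 1. The wording in 8.10.5 is only loose for the tirzepatide arm. Nor is the same gap shown after premature discontinuation: section 9.3.8 mirrors the V4 assessments but does not say whether devices are collected.

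**Conclusion.** The point holds as a minor matter of safety logistics. For a nominal 14 days, up to 21 participants in the tirzepatide arm are still in adverse-event follow-up that includes DKA while the drug washes out, without the study-supplied means for the Annex 5 check or for criterion 4.

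It would be wrong to infer that DKA goes undetected or that any result is biased. DKA treated in a facility and the stopping rule in section 9.2.5 do not depend on the meter, efficacy is untouched, and controls have no scheduled contact after week 16, so no between-arm comparison changes.

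The size rests on three assumptions: treatment ends at V4, as Table 1 and section 9.3.6 have it; the 4.8% DKA figure is annual; and ketosis managed at home is not some 26 to 32 times as frequent as that. On these, well under one event is expected. How many participants own a meter is not stated. The case for change is that a stated preventive measure can be kept in place almost for free: a single-patient meter frees nothing for reuse when it is returned.

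**What to change.** For the tirzepatide arm:
- Remove ketone meters from the V4 return row in Table 1, and except them in the device-return sentence of section 9.3.6.
- Let participants keep the meter, with enough strips handed over at V4, until P3 is complete. Then have it returned by post or written off in the accessories accountability log.
- At P3, ask for any ketone readings since V4.
- Name the same return point in section 8.10.5.

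This reduces the gap to zero. Sample size, power and type I error do not change. The cost is one table row, two short text edits, a few strips per participant and one question on a call that is already scheduled. The downside is postal return or write-off of up to 21 meters, with the log adapted accordingly.
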